## Efficacy and safety

11

Efficacy and safety of surgical procedures will be assessed basing on pathology report, postoperative period data ‐ morbidity and mortality. Safety analysis is performed every 100 enrolled patients. Deviation of morbidity and mortality or frequency of adverse events for more than 30% in extended dissections group will be discussed at steering committee meeting and decision whether to continue or stop the trial will be made.

Surgery risks, preferable approach and conversion decision is surgeon's responsibility.

Adverse event is understood as any unwanted medical deviation in a patient receiving any kind of treatment not necessarily associated with the treatment. In current study adverse event is any unfavourable or unwanted deviation including laboratory tests or condition not necessarily associated with the surgery. Adverse event ‐ any change from preoperative state of a patient, including exacerbation of co‐morbidities.

Serious adverse event ‐ any adverse event resulting in: death, life‐threatening condition, requiring hospital admission or prolongation of in‐hospital treatment, permanent disability or incapacity.

Hospital admissions or deaths due to progression of the disease are not considered to be serious adverse events. Adverse events are described and rendered in eCRF. Relation of adverse events to surgical procedure is determined by investigator. Adverse events classification is performed in accordance with CTCAE ver. 4·0 terminology.

Any treatment or observation in case of adverse event is prescribed by attending doctor, who is responsible for it.

## Follow‐up

12

Schedule of necessary investigations and follow‐up visits is in *Appendix*
S3 (supporting information).

Visit day date deviation: 30 day visit +/‐ 2 days, other visits ‐ +/‐ week. Data on completed visits is transferred to eCRF in 5 working days. Quality of life is assessed via questionnaires filled in before surgery, on day 30, 3‐month visit, 1, 3 and 5‐year visits.

To minimize number of patients lost for follow‐up patients are able to provide results of their routine follow‐up investigations and get a consult of expert centre, which will facilitate patients' adherence to follow‐up.

## Data quality

13

To provide high quality of data regular on‐site monitoring visits will be arranged.

Data is entered to electronic CRF and after the visit is marked as complete data is verified during monitoring visit.

Monitoring visits are scheduled according to number of visits ready for verification. Date of the visit is agreed with centres in advance.

Before initiation of the trial an interactive training is conducted and a test electronic database is created for familiarization with the system and test data entry.

During monitoring visits primary medical documentation and eCRF data are matched. After verification of the data it can be exported for the analysis.

Monitors also ensure the consent, ethical committee approval and other relevant documents are present.

Data of all patients is monitored. First monitoring visits are verifying 100% of data, after analysis of monitoring visits «risk assessment monitoring» may be introduced.

In case of any problems with trial conduct in a centre monitors facilitate resolving of such problems.

**Table nlm-table-wrap-3:** Superiority by a Margin Test for the Difference of Two Exponential Hazard Rates Analysis

Numeric Result with Ha: h2 < h1 ‐ Δ and Uniform Accrual											
	Total Sample Size	Control Sample Size	Trtmnt Sample Size	Control Hazard Rate	Trt Hazard Rate	Clin'l Super'ty Bndry	Control Loss Hazard Rate	Trtmnt Loss Hazard Rate	Accrual Time	Follow Up Time	
Power	N	N1	N2	h1	h2	B	ω1	ω2	R	T‐R	Alpha
0,8004	768	384	384	0,139	0,102	0,139	0,165	0,165	3,0	5,0	0,050
Second Section of Numeric Report											
	Total Events	Control Events	Trtmnt Events	Prop'n Control N1/N	Hazard Rate Diff h2‐h1	Hazard Ratio h2/h1	Clin'l Super'ty Margin	Clin'l Super'ty Ratio	Var'nce of h1 hat	Var'nce of h2 hat	
Beta	E	E1	E2	P1	D	HR	Δ	r	σ^2^(h1)	σ^2^(h2)	
0,1996	270	150	120	0,500	‐0,036	0,737	0,000	1,000	0,049	0,033	

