**Table nlm-table-wrap-2:** 

Title:	Multicentre randomized controlled trial of oncological outcomes of D3 lymph node dissection in colon cancer
Study design:	*Patients with primary resectable colon cancer included in the trial are randomized into two groups for D2 (group I) and D3 (group 2) dissection*
Aims and endpoints:	*Aim of the study*: To determine if long‐term outcomes of D3 lymph node dissection in colon cancer are superior to D2 lymph node dissection *Primary endpoint*: Overall survival (time frame: 5 years after last patient enrolment)
	*Secondary endpoints*: Disease‐free survival (time frame: 5 years after last patient enrolment)
	Short‐term outcomes (time frame: 30 days after operation) Lymph node metastasis pattern (number of lymph node with metastases related to number of lymph nodes studied) CME quality (ratio of good, satisfactory and unsatisfactory quality) Lymph node yield (number of lymph nodes removed) Quality of life of patients
**Patients:**	*Male and female patients over 18 years old, who signed informed consent, with diagnosed primary colon cancer T1‐4a N any M 0‐1 (in case of resectable metastases)*
**Number of patients**	*768 (384 + 384)*
**Study duration:**	*The study is conducted starting from January 15 2017 until target number of patient is enrolled and 5 years of follow‐up after enrolment of the last patient*
**Estimated time until target number of patients is reached:**	*3 years*
**Statistical analysis**	*With ά value of 0,05 and β – 0,8, 768 patients enrolment is planned to determine statistical superiority of overall survival after D3 lymph node dissection over D2 dissection with assumed 10% increase in survival with 3 years accrual period and 5 years of follow‐up*

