## Sample size calculation and statistical analysis

15

To determine the sample size current data from national cancer registry was used^33^, according to which 5 year survival of colon cancer patients is 50%. Survey among surgeons revealed anticipated improvement of survival due to D3 lymph node dissection of 10%. For sample size calculation MedCalc software was used (function of sample size calculation for survival analysis (log rank test) using D. Machin method^34^), according to current survival data, sample size was determined as 762 patients. Using sample size calculation for superiority study via PASS software with C. Chow et al and J. Lachin et al method^35^, ^36^, with α – 0,05 and β – 80%, with 15% of patients lost for follow‐up in case of 3 year accrual period and 5 year follow‐up sample size was determined as 768 patients. As sample sizes obtained by different methods were similar the greater number was used to determine the sample size as 768 patients.

“Intent‐to‐treat” analysis will be performed, thus once randomized patients will be analysed in their randomization group, irrespective of actually received treatment.

For statistical analysis of primary endpoint (overall survival during the study period) Kaplan–Meier method will be implied as the probability of patients survival depends only on time after surgery, as there is no anticipated change of survival during the trial conduct. To compare survival curves long‐rank test will be used.

For secondary endpoints type of analysis will depend on the nature of data. For disease‐free survival (survival without local or distant recurrence during the study period) Kaplan–Meier curves will be used with the long‐rank test. For analysis of short‐term outcomes (morbidity and mortality), lymph node yield parametric and non‐parametric criteria will be used to compare mean values and contingency tables.

For categorical data, to assess the significance of association of two kinds of classification (contingency tables) exact Fisher's test will be implied by default as it can be used when sample distribution is only approximately equal to theoretical distribution and therefore this test is universal. For the final analysis as the sample reaches calculated size Pearson Chi square test will be used.

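### The 80% power quoted for 768 patients belongs to an undeclared one-sided 5% test, whereas the companion figure of 762 reproduces only as a two-sided 5% calculation

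*Protocol article*

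**What the plan says.** Section 15 derives the sample size twice, from 50% five-year survival under D2 and a hoped-for gain of 10 percentage points.

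- The first calculation uses a log-rank function in MedCalc: "sample size was determined as 762 patients". That sentence gives no alpha, power or loss rate.
- The second uses PASS, "with α – 0,05 and β – 80%, with 15% of patients lost for follow‐up", with 3 years of accrual and 5 years of follow-up, and gives 768.
- The choice between them is explained thus: "As sample sizes obtained by different methods were similar the greater number was used to determine the sample size as 768 patients".

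The PASS output is printed at the end of section 13 (Data quality) under the title "Superiority by a Margin Test for the Difference of Two Exponential Hazard Rates Analysis". Its results are headed "Numeric Result with Ha: h2 < h1 ‐ Δ and Uniform Accrual", the margin is 0.000, and the main row reads "0,8004 768 384 384 0,139 0,102 0,139 0,165 0,165 3,0 5,0 0,050" (power, total and arm sizes, hazards, boundary, loss hazards, accrual, follow-up, alpha). The second row gives 270 events (150 + 120), a hazard ratio of 0.737, variances of 0.049 and 0.033, and beta 0.1996.

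The synopsis (section 4) repeats the claim: "With ά value of 0,05 and β – 0,8, 768 patients enrolment is planned". Neither the synopsis, nor the planned log-rank test, nor the closing rule in section 15 for concluding that D3 is superior states a number of sides.

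**The concern.** A power figure means something only together with the test it belongs to. The table's alternative points in one direction, so its alpha of 0.050 is a one-sided error rate. A log-rank test judged by the usual two-sided p-value against 0.05 is stricter, and the printed 80% would not apply to it. The two sample sizes also look like independent support for one another, which they are only if they share an error rate and a loss assumption.

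What is at stake is the primary conclusion. With sidedness open, a result favouring D3 with a one-sided p-value between 0.025 and 0.05 is positive on one reading and negative on the other. Under one-sided 0.05, the chance of wrongly declaring D3 superior is 5%; under two-sided 0.05, it is 2.5% in that direction.

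**Working it through.** **Inputs.** Five-year survival of 50% and 60% (section 15); 384 per arm, loss hazard ω = 0.165 per year in both arms, uniform accrual over 3 years, 5 further years of follow-up, alpha 0.050 (table in section 13).

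**Step 1: reproduce the PASS row.**

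- Hazards: h1 = ln 2 / 5 = 0.1386; h2 = −ln 0.6 / 5 = 0.1022; difference 0.03646; ratio 0.737.
- Probability of an observed death, with s = h + ω: P = (h/s) × [1 − (e^(−5s) − e^(−8s)) / (3s)].
- D2: s = 0.3036, P = 0.391, deaths = 384 × 0.391 = 150.1. D3: s = 0.2672, P = 0.313, deaths = 120.3. Total 270.4 (table: 150 + 120 = 270).
- Variances h²/P: 0.0492 and 0.0333 (table: 0.049 and 0.033).
- Expected test statistic: 0.03646 / √[(0.0492 + 0.0333)/384] = 2.488.
- One-sided 0.05: Φ(2.488 − 1.645) = **0.8004**, the printed value.
- Two-sided 0.05: Φ(2.488 − 1.960) = **0.701**. Other formulas agree: 0.7035 with a pooled null variance, 0.708 by Schoenfeld on 270 deaths, 0.701 by Freedman on 270 deaths.

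**Step 2: reproduce 762.** Freedman deaths = (z_α + z_β)² × [(1 + HR)/(1 − HR)]², with HR = 0.737 and 80% power. The average death probability is 1 − (0.50 + 0.60)/2 = 0.45. No loss allowance is made.

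| Test level | Deaths | Deaths / 0.45 | Rounded up per arm |
|---|---|---|---|
| two-sided 0.05 | 342.3 | 760.6 | 2 × 381 = **762** |
| one-sided 0.05 | 269.6 | 599.1 | 2 × 300 = 600 |

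Only the two-sided version returns 762.

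**Step 3: compare the two sizes.** The 762 rests on a two-sided test, no loss and about 343 deaths. The 768 rests on a one-sided test, heavy loss and 270 deaths. The easier test lowers the requirement and the loss raises it, and the two differences nearly cancel.

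**Step 4: dependence on the loss rate.** The hazard of 0.165 is close to 15% per year (−ln 0.85 = 0.1625). In the Step 1 model it removes ω/s × [1 − (e^(−5s) − e^(−8s)) / (3s)] of patients before death: about 47% in D2 and 51% in D3. Section 15 speaks only of 15% of patients lost. Taking that, as an assumption, to mean 15% over 5 years gives ω = −ln 0.85 / 5 = 0.0325. Then deaths are 207.7 + 169.1 = 376.8 and the expected statistic is 2.936. Two-sided power is Φ(2.936 − 1.960) = **0.835** (Schoenfeld 0.842).

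**Step 5: deaths needed for 80% power at two-sided 0.05.** About 337 (Schoenfeld) to 343 (Freedman). Under the printed loss hazard these correspond to about 960 and 974 patients respectively.

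**The case against.** The best defence is that the table discloses its direction, the aim is superiority of D3, and the rule for concluding superiority is itself directional. A one-sided 5% test is a coherent reading of table and rule together, and on that reading 80% is correct. This stands. It means the 70% describes a test the protocol has not committed itself to, just as the 80% describes one it has not declared. The number of sides is also something an analysis plan might fix. Even so, the protocol relies on a power figure tied to one choice and sets beside it a calculation that reproduces only under the other.

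Three stronger readings are tempting and are not supported.

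- A reader might infer that the trial has only 70% power, or needs 974 patients. Both follow only if the test is two-sided and the loss hazard really is 0.165 per year. On the 15%-over-5-years assumption, 768 patients exceed 80% two-sided power.
- A reader might infer that the protocol states one alpha for both calculations. It does not: the sentence on 762 gives none, and its two-sidedness is an inference from an exact numerical match.
- A reader might infer that the protocol offers the similarity as formal validation. It only calls the sizes similar and takes the larger, which is cautious in itself. The fault is that the two are not comparable.

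Printing 80% as beta in section 15 and the synopsis is a labelling slip; the table has beta as 0.1996.

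**Conclusion.** The point holds as a mismatch between a relied-on power figure and an undeclared test. The 0.8004 at 768 patients is a one-sided 0.05 figure, reproduced to four decimals. At two-sided 0.05 the printed row gives about 70%, a loss of some 10 percentage points. The 762 is, by inference, a two-sided 0.05 figure without loss, so its closeness to 768 supports neither.

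The size for the trial itself depends on the loss assumption: two-sided power at 768 is about 70% with the printed hazard, and about 83.5% if 15% loss over 5 years is assumed. All these figures also assume exponential survival, 50% versus 60% at five years, and the stated accrual and follow-up. The point is worth correcting before analysis because it touches the primary conclusion and costs little.

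**What to change.** 1. In section 15 and the synopsis, declare the sidedness and level of the primary log-rank test. Two-sided 0.05 is preferable because it matches the 762 calculation; if one-sided 0.05 is intended, say so and justify it.
2. Settle what 15% loss means (per year, or in total and over what period).
3. Rerun the PASS calculation once at the declared level with that loss rate. Replace the table and restate the power and expected deaths for 768 patients. If the test is two-sided, give the requirement of about 337 to 343 deaths for 80% power.
4. Remove the sentence that relies on the similarity of 762 and 768.
5. Write power 80% (beta 0.20) in both places.

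The cost is wording and one rerun. The correction adds no patients. Its only downside is that the stated power may become less favourable: about 70% if the printed loss hazard is confirmed and the test is two-sided.

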## Collection, storage and sharing of data

14

Clinical data (demographics, diagnosis, investigations, surgery data, pathology, lab results etc.) is entered to eCRF basing on primary medical documentation (patient file, outpatient file, investigation reports, laboratory reports, operation notes etc.). For assessment of quality of life validated questionnaires EORTC QLQ‐C30 and colorectal module CR 29. Questionnaires are filled in during visits (face to face or on the phone).

Data in eCRF is stored under a pseudonym with password‐protected access on the server of main study centre. Data is stored for at least 15 years after the end of the study. Investigators have access to their centre's patients data, coordinating investigator and monitors have access to all patients' data.

Full access to final database will be available for coordinating investigator, access to centre's database is provided for relevant principal investigators on demand.

After verification data is exported for statistical analysis using SPSS software.

Publications in relevant journals of protocol, first safety report, short‐term results after enrolment is finished and final publication, when primary end‐point is reached, are planned. This data will also be shared among specialists via presentations on conferences.

## Sample size calculation and statistical analysis

15

To determine the sample size current data from national cancer registry was used^33^, according to which 5 year survival of colon cancer patients is 50%. Survey among surgeons revealed anticipated improvement of survival due to D3 lymph node dissection of 10%. For sample size calculation MedCalc software was used (function of sample size calculation for survival analysis (log rank test) using D. Machin method^34^), according to current survival data, sample size was determined as 762 patients. Using sample size calculation for superiority study via PASS software with C. Chow et al and J. Lachin et al method^35^, ^36^, with α – 0,05 and β – 80%, with 15% of patients lost for follow‐up in case of 3 year accrual period and 5 year follow‐up sample size was determined as 768 patients. As sample sizes obtained by different methods were similar the greater number was used to determine the sample size as 768 patients.

“Intent‐to‐treat” analysis will be performed, thus once randomized patients will be analysed in their randomization group, irrespective of actually received treatment.

For statistical analysis of primary endpoint (overall survival during the study period) Kaplan–Meier method will be implied as the probability of patients survival depends only on time after surgery, as there is no anticipated change of survival during the trial conduct. To compare survival curves long‐rank test will be used.

For secondary endpoints type of analysis will depend on the nature of data. For disease‐free survival (survival without local or distant recurrence during the study period) Kaplan–Meier curves will be used with the long‐rank test. For analysis of short‐term outcomes (morbidity and mortality), lymph node yield parametric and non‐parametric criteria will be used to compare mean values and contingency tables.

For categorical data, to assess the significance of association of two kinds of classification (contingency tables) exact Fisher's test will be implied by default as it can be used when sample distribution is only approximately equal to theoretical distribution and therefore this test is universal. For the final analysis as the sample reaches calculated size Pearson Chi square test will be used.

Prior to comparing of group mean values in case of quantitative data, a non‐parametrical criterion of Shapiro Wilks will be used to test the normality of distribution. In case of normal distribution Student's criterion for independent samples will be used (dependant samples for quality of life assessment). For data not distributed normally non‐parametric Mann–Whitney U criterion will be implied.

Lymph node metastases pattern will be assessed as calculation of frequency of affected nodes related to number of studied nodes in each group. Correlation analysis of association of size, T‐stage, localization of the tumour with affected groups of lymph nodes, frequency of metastases, tumour budding grade, lymphovascular and perineural tumour invasion. Spearman rank correlation coefficient will be used as the data may be distributed not normally and numeric data may be included. To assess correlation of quantitative data distributed normally Pearson correlation coefficient will be implied.

For the primary endpoint and disease free survival missing data will be handled according to the survival analysis nature – censoring of the patient with the date of last contact.

Missing data for the secondary endpoints will be dealt with by using multiple imputations with Markov chain Monte Carlo method (monotone method if the data shows a monotone pattern of missing values; otherwise, fully conditional specification).

Conclusion of superiority of D3 lymph node dissection will be made in case of statistical superiority of survival during the study of D3 group over D2.

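### Section 15 states 15% loss to follow-up, but the PASS row behind N = 768 uses a loss hazard of 0.165 per year, which loses about 49% of patients; the mismatch is conservative, but text and table must be reconciled

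*Protocol article*

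**What the plan says.** Section 15 (Sample size calculation and statistical analysis) takes registry data that "5 year survival of colon cancer patients is 50"% and a surgeons' survey giving an "anticipated improvement of survival due to D3 lymph node dissection of 10"%. It reports two calculations:

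- a MedCalc log-rank calculation, giving 762 patients;
- a PASS superiority calculation "with α – 0,05 and β – 80"%, "with 15% of patients lost" to follow-up, "in case of 3 year accrual period and 5 year" follow-up, giving 768 patients.

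The section calls the two results similar and adopts the larger. The loss figure carries no time unit.

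The PASS output is printed as a table at the end of section 13 (Data quality). Its column "Control Loss Hazard Rate" and the matching treatment column both hold 0.165. The rest of the row gives h1 = 0.139, h2 = 0.102, accrual 3.0, follow-up 5.0, alpha 0.050 and the one-sided alternative h2 < h1 − Δ with Δ = 0. The results are 384 + 384 patients, 150 + 120 = 270 events, variances 0.049 and 0.033, and power 0.8004.

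**The concern.** The loss hazard sits in the same row as the death hazards, so it is on the same yearly scale, and there 0.165 exceeds the control death hazard of 0.139. Read beside accrual and follow-up times, a share of patients lost is most naturally a total over the study. The table appears to assume something much larger.

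This row is the only place in the protocol that gives expected deaths and power for overall survival. If its loss input is not the one the text describes, a reader cannot tell how many deaths the design expects, or how much power 768 patients give under the stated assumption.

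**Working it through.** **Inputs.** From section 15: 5-year survival of 50% and 60%. From the PASS table: uniform accrual R = 3, T − R = 5 (so T = 8), 384 per arm, one-sided 0.05, loss hazard ω = 0.165.

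**Time scale.** h1 = −ln(0.50)/5 = 0.1386 and h2 = −ln(0.60)/5 = 0.1022, matching the table's 0.139 and 0.102, so hazards are per year. Then 1 − exp(−0.165) = 0.152, that is 15.2% lost each year.

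**Formulas** (exponential death and loss, uniform accrual, unpooled variance), with g = h + ω:

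- A = 1 − [exp(−5g) − exp(−8g)]/(3g)
- P(death observed) = (h/g)·A and P(lost before death or study end) = (ω/g)·A
- variance of each hazard estimate, per patient = h²/P(death)
- power = Φ(|h1 − h2|/SE − z), with SE = √[(σ1² + σ2²)/384]

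**Reproducing the printed row, ω = 0.165:**

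| | D2 | D3 |
|---|---|---|
| g | 0.3036 | 0.2672 |
| A | 0.856 | 0.819 |
| P(death) | 0.391 | 0.313 |
| Deaths in 384 | 150.1 | 120.3 |
| Variance | 0.049 | 0.033 |
| P(lost) | 46.5% | 50.6% |

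Total deaths are 270.4. SE = √(0.08248/384) = 0.01466, and 0.03646/0.01466 = 2.488. Power = Φ(2.488 − 1.645) = 0.8004, and the N for 80% power is 768. Every printed figure is matched, using the unrounded death hazards. Average loss is (46.5 + 50.6)/2, about 49%, against 270.4/768 = 35% observed to die.

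**The same formulas with 15% lost in total.** The text does not say over what period, so three readings are shown:

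| Reading of 15% | ω per year | Deaths at N = 768 | Power, one-sided 0.05 | Power, two-sided 0.05 | N for 80%, one-sided / two-sided |
|---|---|---|---|---|---|
| By 8 years: −ln(0.85)/8 | 0.020 | 390 | 0.91 | 0.85 | 534 / 678 |
| By 5 years: −ln(0.85)/5 | 0.0325 | 377 | 0.90 | 0.84 | 552 / 700 |
| Actually lost in study, death competing | 0.037 | 372 | 0.90 | 0.83 | 558 / 708 |

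None of these gives 270 deaths, power of 0.80 or N = 768.

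**15% per year.** ω = −ln(0.85) = 0.1625 gives 272 deaths and N = 764 at one-sided 0.05, close to the printout. This suggests, but does not prove, that 15% was entered as an annual rate.

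**The MedCalc figure.** Freedman's formula with HR = 0.102/0.139, unrounded 0.737, two-sided 0.05 and 80% power needs 343 deaths. With an average 5-year death probability of (0.50 + 0.40)/2 = 0.45, N = 343/0.45 = 762. So 762 is consistent with a two-sided log-rank calculation with no allowance for loss, whereas 768 is one-sided with about 49% loss.

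**The case against.** The best defence is that the PASS row is not miscalculated and that section 15 never says the 15% is cumulative. If 15% per year was meant, deaths, power and N all stand and only two words are missing. That is fair: the documents do not settle which was intended. But the total reading is the more natural one, and on the annual reading the text still fails to tell the reader that about half the patients are expected to be lost. Section 12, for its part, describes measures to minimise loss. Text or table has to change on either reading.

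A second defence is that the mismatch is harmless to the sample size. This largely stands. Under 15% total loss, 768 patients exceed the 80% target one-sided and two-sided. N also does not rest on this row alone: a PASS result below 762 would, under the protocol's own rule of taking the larger figure, give 762, a change of 6 patients.

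Three stronger readings are tempting and not supported:

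- A reader might infer that the loss rate leaves the trial with 70% power. That figure (and an N of 974) arises only if the 0.165 hazard is kept and the test is made two-sided. The drop from 0.80 to 0.70 comes from the sidedness, not from the loss rate.
- A reader might infer that 270 deaths decides when the data are mature. Nothing in the protocol uses it that way: the endpoint's time frame is 5 years after the last enrolment, and the only periodic look described is the safety review every 100 patients.
- A reader might infer that 768 should be cut to between 534 and 708. The separate MedCalc figure and the take-the-larger rule speak against that.

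**Conclusion.** The point holds as an inconsistency between text and table. Section 15 states 15% of patients lost; the row that produced 768 assumes about 49%. If the total is 15%, expected deaths are about 372 to 390 rather than 270, and power is about 0.90 to 0.91 one-sided (0.83 to 0.85 two-sided) rather than 0.80. The direction is conservative, and this mismatch does not make the trial underpowered. These figures assume exponential death and loss, uniform 3-year accrual and equal loss hazards in both arms, as in the PASS row.

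The similarity of 762 and 768 is not corroboration, because the two calculations appear to differ in both sidedness and loss allowance. That inference about MedCalc rests on matching the number, since its settings are not printed.

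**What to change.** Keep N = 768 and reconcile section 15 with the PASS table in one of two ways:

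- **If 15% is the total loss:** state the period it covers, rerun PASS with the matching hazard (0.020 to 0.037 per year), and restate expected deaths (about 375) and power, naming the sidedness of alpha.
- **If 15% per year was meant:** say so in section 15, state that about half the patients are expected to be lost, and give 270 deaths with power 0.80 one-sided, or 0.70 if the test is two-sided.

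In either case, remove the sentence that uses the similarity of the two sample sizes as support, or state each calculation's sidedness and loss allowance beside it.

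The cost is at most one rerun and a corrected paragraph and table, with no change to enrolment.
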